#### Generalization Measures Analysis

##### Psychological Questionnaires

We will calculate and extract total scores and subscores of the psychological questionnaires (SF-36 walk-wheel [48], COMPAS-W [49] SAI [50], BDI [51], MOS-SS [66], and NPS [52]) for further analysis (see the Reliable Change Index subsection below).

##### Resting-State EEG

We will analyze resting-state EEG data using custom scripts based on the EEGLAB toolbox [43] functions in MATLAB. We will apply a band-pass filter (1-30 Hz) to the EEG data after downsampling to 250 Hz. Then, the EEG data will be rereferenced to the average of all 24 electrodes. We will use an artifact subspace reconstruction [67] method with default parameters for denoising and removing movement artifacts. Subsequently, we will use power spectral density to estimate the intended frequency band powers (ie, theta, alpha, and high beta) from the cleaned data. Finally, we will extract the frequency band power values for further analysis (see Reliable Change Index below).

##### Neuroimaging

We will analyze the acquired spectra using the Java-based magnetic resonance user interface (jMRUI version 6.0; MRUI Consortium). First, we will remove the dominant water resonance using the Hankel Lanczos singular valve decomposition algorithm. The ON and OFF spectral subsets will be summed, producing single ON and OFF 68-ms subspectra for each spectra dataset. These 68-ms subspectra will then be subtracted, resulting in GABA-edited difference spectra to measure GABA concentration at 3.01 ppm. We will quantify GABA using AMARES, a nonlinear least-squares fitting algorithm operating in the time domain. Peak fitting for GABA will be performed after manually defining the center frequency and line width of the GABA peak and modelling the GABA peak as a singlet. We will use Lorentzian curves to obtain the peak amplitude for this resonance. The OFF spectral subsets will be summed, producing single OFF 68-ms subspectra for each spectra dataset to measure creatine concentration at 3.02 ppm. We will then phase the single OFF 68-ms subspectra with respect to both the zero- and first-order phase. Spectral fitting in AMARES will be performed after manually defining the center frequency and line width of the creatine peak and modelling the creatine peak as a singlet. We will use Gaussian curves to obtain the peak amplitude for this resonance. Lastly, the GABA to creatine ratios will be calculated and extracted for further analysis (see Reliable Change Index below).

##### Reliable Change Index

We will evaluate changes in generalization measures such as power spectral density, GABA to creatine ratios, and total scores and subscores of the psychological questionnaires using the Reliable Change Index (RCI) [68,69]. We will use the RCI to evaluate the reliability of change over time for individual data. This index indicates whether the change score between 2 time points (eg, pre- and postintervention) for the same individual is considered clinically significant.

RCI is a ratio of the actual observed difference by the standard error of the difference (SE_diff_): RCI = [M_post_ – M_pre_]/SE_diff_, and SE_diff_ = SD√2(1 – r), where SD is the standard deviation of the measurement and r is the reliability coefficient of the measure.

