#### Psychological Questionnaires

Participants will complete the 36-item Short Form Health Survey modified for SCI (SF-36 walk-wheel) [48], the COMPAS-W Scale of Wellbeing [49], the State Anxiety Inventory (SAI) [50], the Beck Depression Inventory (BDI) [51], and the Medical Outcomes Study Sleep Scale (MOS-SS) [52]. These questionnaires are self-report measures. The SF-36 [48] is a frequently used instrument that measures global health-related quality of life. The SF-36 [48] consists of 8 scales: physical functioning, physical role functioning, bodily pain, general health perceptions, vitality, social role functioning, emotional role functioning, and mental health. Higher scores represent a better health status. The 26 items of the COMPAS-W [49] scale measures both subjective and psychological well-being. It consists of 6 subscales, which provide an indication for different aspects of well-being: composure, own worth, mastery, positivity, achievement, and satisfaction. Higher scores represent higher levels of well-being. The 20-item SAI [50] assesses state anxiety, with higher scores indicating greater anxiety. The 21-item BDI [51] is used to assess the severity of depressive symptoms, with a higher score indicating a greater number of depressive symptoms. The 12-item MOS-SS [52] assesses 6 key factors of sleep: sleep initiation, maintenance, respiratory problems, quantity, perceived adequacy, and somnolence. Higher scores reflect more sleep quality and quantity. Lastly, we will use the Neuropathic Pain Scale (NPS) [53] to evaluate the specific qualities of SCI neuropathic pain, such as sharp, hot, dull, cold, and sensitive.

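### The Reliable Change Index is said to show clinical significance, but as defined it can show only that a change exceeds measurement error

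*Protocol article*

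**What the plan says.** The section Reliable Change Index, under Generalization Measures Analysis in the protocol article, gives the index two meanings in consecutive sentences. The first is its purpose: "We will use the RCI to evaluate the reliability of change over time for individual data". The second is how a result is to be read: "This index indicates whether the change score between 2 time points (eg, pre- and postintervention) for the same individual is considered clinically significant".

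The definition follows. The RCI is the post-minus-pre difference over SE_diff, and SE_diff is formed from two quantities: "SD is the standard deviation of the measurement and r is the reliability coefficient of the measure".

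The scope is wide. The index is to be applied to "power spectral density, GABA to creatine ratios, and total scores and subscores of the psychological questionnaires using the Reliable Change Index". The section Psychological Questionnaires under the same analysis heading confirms this for the self-report measures: "We will calculate and extract total scores and subscores of the psychological questionnaires". The sections Resting-State EEG and Neuroimaging also pass their extracted values on to the RCI.

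**The concern.** Whether a change is distinguishable from measurement error and whether it matters to the patient are separate questions. The first needs the precision of the instrument. The second needs an outside reference, such as a minimal important difference, a normative cut-off or a patient-reported anchor. The article supplies only the first and names the result as if it answered the second.

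The wording carries weight because the RCI is the only analysis the article gives for several stated aims. The Objectives section asks whether the intervention improves mood, sleep, quality of life and well-being, and what neural mechanisms lie behind any effect. If the sentence is followed literally, a participant whose score, band power or metabolite ratio moves by more than measurement error is recorded as having had a clinically significant change. Nothing in the article would support that conclusion.

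**Working it through.** The article states no RCI cut-off, SD or reliability for any measure, so it has no figure to reproduce. The check has three steps.

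**Step 1: what the formula contains.**
- RCI = (M_post − M_pre) / SE_diff.
- SE_diff = SD × √(2(1 − r)). The formula is printed without a visible bar over the radical. I take the root to cover the whole of 2(1 − r) and treat the print as a typesetting matter.
- The inputs are therefore the observed difference, SD and r. None of them is a clinical threshold or a patient anchor.

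**Step 2: what that does to the bar for clinical significance.** With cut-off c, the smallest flagged change is c × SD × √(2(1 − r)). Both c and r are assumptions here. I use c = 1.96 with 1.645 and 2.576 as the range, and r from 0.70 to 0.95.

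At c = 1.96:
- r = 0.95: 1.96 × √0.10 = 1.96 × 0.3162 = 0.62 SD
- r = 0.90: 1.96 × √0.20 = 1.96 × 0.4472 = 0.88 SD
- r = 0.80: 1.96 × √0.40 = 1.96 × 0.6325 = 1.24 SD
- r = 0.70: 1.96 × √0.60 = 1.96 × 0.7746 = 1.52 SD

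For the two ends of the r range at the other cut-offs:
- c = 1.645: 0.52 SD (r = 0.95) and 1.27 SD (r = 0.70)
- c = 2.576: 0.81 SD (r = 0.95) and 2.00 SD (r = 0.70)

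The ratio between the two ends does not depend on the cut-off: √(0.60 / 0.10) = √6 = 2.45. A change of 1.0 SD, at 1.96, would be called clinically significant on a scale with r = 0.90 or 0.95 and not on one with r = 0.80 or 0.70. The difference comes entirely from the precision of the instruments. The error can run both ways: a small change on a very reliable scale acquires the label, and a change that matters on a less reliable scale may be denied it.

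**Step 3: whether a clinical criterion stands elsewhere in the article.**
- The outcome section on the psychological questionnaires describes what each instrument measures and, for most of them, the direction of scoring. For the state anxiety scale, for example, it says that it "assesses state anxiety, with higher scores indicating greater anxiety". It gives no minimal important difference or clinical cut-off.
- The sections on EEG and neuroimaging describe acquisition, processing and extraction only.
- The Patient Global Impression of Change is collected after the 20 sessions, but the article uses it for perceived change in pain and does not connect it to the RCI.

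No criterion was found that could justify the clinical label for any generalization measure.

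**The case against.** The best defence is that this is one loose sentence in a section that otherwise gets the idea right. The sentence before it gives the purpose correctly, the name of the index says reliable change, and the analysis sections that feed into it use only that name. Nowhere does the article say in terms that results will be reported as clinically significant. The sources cited for the method, which are not at hand, may also set out a further clinical criterion. This limits how much harm can be predicted, but it does not rescue the sentence. The sentence is the article's only statement of what an RCI result shows, and it does not follow from the formula printed after it. A statistical analysis plan could add a cut-off, but the meaning assigned here would still be wrong.

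A second point is that these are generalization measures. They do not enter the primary outcome (pain intensity) or the secondary outcome (pain interference), nor the visual and Tau-U analyses of those outcomes. That stands in full and keeps the point modest.

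A reader might also infer something stronger: that applying the index to so many totals and subscores will yield several chance findings presented as generalized benefit, and that replication across participants ought to be required. The documents do not support this. Any count of chance flags depends on a cut-off that the article does not state, on how many scores are counted and on which time points are contrasted. For illustration, 28 scores in 3 participants make 84 indices for one contrast. With no true change, 84 × 0.05 = 4.2 flags are expected at 1.96, but only 84 × 0.01 = 0.84 at 2.576, and about half of either number would point to worsening. The article has no rule that turns isolated flags into a claim of generalization. It assigns the index to individual data and plans its consistency analysis for the primary and secondary outcomes. The cut-off, the key scores and any handling of multiplicity for supporting measures are details that an article may leave to the full protocol or analysis plan.

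**Conclusion.** The point holds as an error in the stated meaning of the index. By the article's own formula the RCI shows reliable change and cannot show clinical significance. That conclusion needs no assumption about cut-off, reliability or number of scores.

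The size of the distortion does rest on assumptions. Over reliabilities of 0.70 to 0.95, the change needed to earn the label varies by a factor of 2.45, from 0.62 to 1.52 SD at an assumed cut-off of 1.96. The label is least defensible for EEG band power and GABA/creatine, which the article uses to explore mechanism and for which it offers no clinical scale.

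The consequence is confined to how the generalization measures are interpreted. It should be corrected, but it does not threaten the trial's conclusion on pain intensity or pain interference.

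**What to change.** Replace the sentence on interpretation in the section Reliable Change Index with wording such as: *the index indicates whether the change between two time points in the same individual exceeds measurement error (reliable change)*. Add that a change will be called clinically significant only for an instrument with a separate criterion fixed in advance, and that the term will not be used for EEG band power or GABA/creatine.

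The cost is an edit to the text and the loss of a label: fewer changes can be called clinically significant. Data collection, the RCI formula and the primary and secondary analyses stay as they are.

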## Results

This clinical trial has been approved by the University of New South Wales Human Research Ethics Committee (approval number: HC190411) and the University of Technology Sydney Human Ethics Committee (approval number: ETH19-4090). Additionally, this study is registered through the Australian and New Zealand Clinical Trials Registry (registration number: ACTRN12620000556943). We plan to commence the trial in October 2020 and expect to publish the results by the end of 2021.

## Discussion

### Overview

Preliminary data in support of BCI-N treatment for SCI neuropathic pain have been reported [24,26]. However, further studies are needed to provide more definitive evidence of the effectiveness of this intervention. This clinical trial using SCED methodology has been designed to evaluate the effectiveness of a novel BCI-N treatment for people with neuropathic pain after SCI.

The BCI-N system of this study will address a key limitation of previous EEG neurofeedback interventions, which have mostly relied on a single form of virtual interaction [20,22,24]. Studies have shown greater cortical involvement [32] and pain reduction [28-31] during the interactive engagement with multiple gaming scenarios than with 1 form of virtual interaction. Based on this evidence, we will use a self-developed BCI-N treatment, which consists of 3 interactive virtual scenarios in a goal-directed gaming environment. Further, the BCI-N system used in this study can provide neurofeedback simultaneously on different brain regions, and hence can be individualized to each participant’s needs. For example, for a participant with bilateral pain, both C3 and C4 EEG channels can be targeted, whereas for a participant with unilateral pain, only C3 or C4 will be targeted during the BCI-N intervention. Additionally, the reinforcement and suppression criteria (ie, the baseline thresholds) for the targeted frequency bands can be customized according to the participant’s progress during the intervention. For example, we can change the difficulty of the game by modifying the baseline thresholds as a way to increase motivation.

SCED is a powerful design to establish guidelines for evidence-based interventions [35]. The key to the SCED method with multiple baselines is that the intervention is introduced in a staggered sequence [35], and the outcome of interest, that is, average pain intensity, is measured repeatedly during different phases. The staggered introduction of the intervention allows for drawing conclusions regarding intervention effects distinct from those associated with maturation, experience, learning, or practice [70]. The SCED methodology accounts for potential confounders, such as environment factors, which may affect primary and secondary outcome measures. Unlike traditional group designs, a SCED can address the effects of the intervention at the individual’s level in a controlled and unbiased way by randomly allocating different baseline periods across participants.

Investigating our novel self-developed BCI-N intervention with a SCED and evaluating it with visual and statistical analyses will provide a rigorous methodology for this study. The high internal validity of a well-implemented SCED study allows for the results of the data analyses to draw reliable conclusions about the effectiveness of the intervention [42,71]. Experimental control is established when the effects of the intervention are repeatedly and reliably demonstrated within a single participant or across a small number of participants. In the multiple-baseline design, each participant will be their own control and will provide an instance of the intervention’s effect replication. This within-study replication is the basis of internal validity in SCEDs. By replicating an investigation across different participants, the generalization of the intervention effects can be examined and hence potentially increase the external validity [35]. Additionally, SCEDs are ideal for researchers working with small or very heterogeneous populations in the development and implementation phases of novel research studies. Thus, the SCED with multiple baselines is considered a viable alternative approach to randomized clinical trials for demonstrating the effectiveness of an intervention when the recruitment of large samples is not feasible. [42].

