### Objectives

The primary objective is to evaluate the effectiveness of a multiday course of BCI-N intervention in a gaming environment to provide pain relief for individuals with SCI neuropathic pain. The secondary objective is to assess the intervention’s effectiveness on participants’ pain through pain interference. We will also determine whether the BCI-N intervention improves mood, sleep quality, quality of life, and well-being. Lastly, we will explore the neural mechanisms underlying the effect of a BCI-N intervention on SCI neuropathic pain. In particular, we will measure resting-state EEG and levels of thalamic GABA content pre- and postintervention.

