## Methods

### Study Design

This study will be conducted based on a single-case experimental design (SCED) with multiple baselines across participants. The SCED is a powerful and effective method that is increasingly used in clinical trial designs [33,34] to evaluate preliminary effectiveness of an intervention [35-37]. Indeed, it has been argued that under the right circumstances, highly controlled SCEDs should be considered on par with traditional group-based randomized clinical trials [38]. An important strength of SCEDs with multiple baselines across participants is that it allows one to determine whether any change observed in the dependent variables occurs when, and only when, the intervention is directed at a particular participant [36]. As a result, the individualized findings of a highly controlled SCED trial can be accumulated to produce results equivalent to those found in randomized clinical trials but requires fewer participants for the same power [38,39]. Thus, the SCED approach is particularly useful when recruiting a large number of individuals into a clinical trial is not feasible.

The SCED method is based on assessing the dependent variables (in this case, pain intensity and pain interference) repeatedly for each of the participants across phases. The design of this study will be AB + follow-ups, where A refers to the baseline phase, B is the intervention phase, and both are followed by a follow-up phase. In addition, we will conduct a further follow-up phase 3 months after completion of the intervention. We will conduct and report the SCED study in accordance with the Single-Case Reporting Guideline in Behavioural Interventions (SCRIBE) 2016 Statement [40]. To meet the SCRIBE reporting standards, there must be at least three participants in a SCED with multiple baselines and more than five assessments of each dependent variable in each phase.

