### Participants

We will recruit 3 individuals with complete thoracic SCI (American Spinal Injury Association Impairment Scale A) for this study. Participants need to meet the following inclusion criteria: (1) aged 18 to 80 years, (2) having persistent neuropathic pain for 6 months or longer, (3) having an average pain intensity of 2 or more (out of 10) in the past week on a visual analog scale (VAS; with 0 cm reflecting no pain to 10 cm reflecting the maximum pain imaginable), (4) being medically stable, and (5) demonstrating an ability to use the VAS. With regard to the neuroimaging component of the study, we will exclude individuals who have metal objects inside their body (eg, stents, metal clips, implants, and shrapnel).

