### Procedure

We will randomly assign 3 participants to different baseline durations of the SCED using a simple randomization method [41]. Conventionally, a minimum of 3 baseline observation days are required to establish stability for the dependent variable [42]; however, more observations are preferred. In this study, we will obtain a stable baseline by using 7 days of observation. We will randomly assign each participant to 1 of 3 experimental conditions characterized by the length of the baseline phase. The first participant will have a 7-day baseline, the second participant will have a 10-day baseline, and the third participant will have a 14-day baseline. All participants will start the baseline phase on the same day. Each baseline phase will be followed by 20 days of a 30-minute BCI-N intervention over a 4-week period. Subsequently, there will be a 1-week follow-up for each participant to continue reporting the primary and secondary outcome measures in order to monitor possible changes in pain intensity and pain interference after completion of the intervention. In addition, we will conduct a further 1-week follow-up 3 months after completion of the intervention. Figure 1 summarizes the study procedure.

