### Intervention

Each participant will receive 30-minute daily sessions of the BCI-N intervention for 20 days over a 4-week period in their home. Each session will involve two 15-minute BCI-N interventions divided by a 5-minute break, and each session will start and finish with measurement of the resting-state EEG levels. The BCI-N treatment incorporates an interactive gaming interface (ie, NeuroGame), and a neuromodulation protocol targeted to suppress theta and low alpha (4-8 Hz) and high beta (20-30 Hz) band powers and to enhance high alpha (9-12 Hz) band power (Figure 2). We will acquire the EEG using the EEG system SMARTING device (mBrainTrain; see Figure 2). During the BCI-N intervention, neurofeedback will be provided on SCI neuropathic pain-related regions of the brain, such as C3 and C4 [24]. In particular, the EEG signals will be processed in real time with custom scripts in MATLAB R2020b (MathWorks) using EEGLAB [43] functions. The real-time EEG processing will include extracting the power from the frequencies of interest (ie, 4-8 Hz, 9-12 Hz, and 20-30 Hz) and transferring the information to the NeuroGame interface. The NeuroGame interface was developed using the Unity 3D game engine (Unity Technologies 2019.2.6f1). Our game scenario is based on an online game called A Waffles Fate [44]. We modified the concept from a navigating ghost to a jellyfish. Our scenario, called Floating Jellyfish, provides neurofeedback in an interactive, goal-directed, virtual gaming environment. The visual feedback of the Floating Jellyfish game scenario is as follows: When only 1 EEG frequency band power is suppressed or reinforced as desired, the jellyfish changes color; when 2 frequency band powers are activated correctly, the jellyfish starts to move; and when all 3 band powers are activated, the ocean background changes color, and a seconds timer begins. Points accumulate only for those seconds that the participant keeps all 3 bands activated. The aim of the game is to receive as many points as possible. Points are summed across each 30-minute daily session of BCI-N treatment. Furthermore, the total points scored will be summed across all 20 sessions of BCI-N treatment, with the aim being to accrue as many points in total as possible. The within- and between-session points totals will also provide valuable information about the participants’ experience, engagement, and progression through the game.

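### Staggered baselines control for calendar time and time in study only; the Discussion's claim of controlled, unbiased inference should be narrowed, because expectation and session attention start with treatment in every participant

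*Protocol article*

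**What the plan says.** **Design.** Methods, Study Design: "The design of this study will be AB + follow-ups, where A refers to the baseline phase, B is the intervention phase". Participants: "We will recruit 3 individuals with complete thoracic SCI". Baselines last 7, 10 or 14 days, allocated at random, and Procedure states: "All participants will start the baseline phase on the same day". The comparator is each participant's own baseline. No sham, non-contingent or attention-control phase is described.

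**What starts with phase B.** Intervention: "Each participant will receive 30-minute daily sessions of the BCI-N intervention for 20 days over a 4-week period in their home". These sessions bring the EEG headset and a game with points. The primary outcome is a VAS that participants mark themselves three times a day in a paper diary. Daily contact about the diaries is described without restriction to one phase.

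**What the design is said to deliver.** Study Design gives as a strength that one can determine "whether any change observed in the dependent variables occurs when, and only when, the intervention is directed at a particular participant". The Discussion (Overview) says: "The staggered introduction of the intervention allows for drawing conclusions regarding intervention effects distinct from those associated with maturation, experience, learning, or practice". It also says that the method accounts for potential confounders, giving environmental factors as the example, and that it addresses individual effects "in a controlled and unbiased way by randomly allocating different baseline periods across participants". It ties experimental control to replication across participants, and says that a well-implemented study of this kind supports reliable conclusions on effectiveness.

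**Limitations.** The only limitation named is dropout. A mock session before the trial is offered as its mitigation.

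**The concern.** Staggering works by breaking the link between treatment start and time. If pain falls at a different day for each participant, and each time at that participant's own treatment start, a cause tied to the calendar or to days in study becomes implausible. The argument says nothing about causes that themselves start with treatment.

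Expectation of relief is such a cause. So is the attention that comes with a daily 30-minute session, as distinct from the diary contact that seems to run throughout. Blinding to phase is not possible in this schedule, because participants go from a diary alone to daily headset sessions. A response to that change would appear at the end of 7, 10 and 14 days, would replicate across participants, and would meet the when-and-only-when criterion as well as a specific effect would.

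At stake is how a positive result may be read. The unqualified wording on bias and confounders invites the reader to exclude expectation as an explanation. The design cannot exclude it.

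**Working it through.** The plan states no alpha, power, SD or effect size, so there is no figure to reproduce. The check asks which kinds of influence the planned schedule and indices can tell apart.

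**Inputs from the plan.** Baselines of 7, 10 and 14 days with a common start, then 20 intervention days. Tau is the number of concordant minus discordant pairs, divided by all pairs. The A-to-B pairs number 7×20 = 140, 10×20 = 200 and 14×20 = 280.

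**Assumptions, not in the plan.** Daily VAS mean 5 cm, SD 1 cm, lag-1 autocorrelation 0.3, the 20 treatment days treated as consecutive, 2,000 repetitions. Negative Tau means less pain in phase B.

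**Step 1: what each kind of influence looks like.** Mean Tau for the 7-, 10- and 14-day participants, with a shift or total drift of 1.5 cm:

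| Influence | Tau | Tau after removing baseline trend |
|---|---|---|
| Specific effect, starts with treatment | -0.72, -0.72, -0.71 | -0.72, -0.71, -0.71 |
| Expectation response, starts with treatment | -0.71, -0.71, -0.71 | -0.71, -0.71, -0.71 |
| Common event on day 8 | -0.71, -0.50, -0.35 | -0.71, -0.43, -0.23 |
| Slow drift | -0.33, -0.36, -0.42 | -0.32, -0.34, -0.38 |

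The first two rows agree by construction. Both are a step at the participant's own treatment start, and the small differences are simulation noise. That is the point: the planned data contain nothing that distinguishes them. The pattern is the same at 1 cm (about -0.52 in every participant for both) and at 2 cm (about -0.84 to -0.85 for both). The last two rows show the stagger doing its proper work. An event shared by all participants gives an effect that shrinks as the baseline lengthens, and drift gives a weaker one.

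**Step 2: size under a simpler model.** For independent normal days and a fall of d within-person SDs, expected |Tau| = 2Φ(d/√2) − 1:
- d = 0.5: 2Φ(0.354) − 1 = 0.28
- d = 1.0: 2Φ(0.707) − 1 = 0.52
- d = 1.5: 2Φ(1.061) − 1 = 0.71

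If a one-sided 5% Mann-Whitney test were applied to each participant, a purely non-specific fall of these sizes would be positive in all three participants in about 3%, 45% and 90% of trials (3,000 simulated trials for each d). With no fall the figure is about 0%. That test is not in the plan, so these rates only illustrate scale.

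**Step 3: the plan's other criteria.** Data Analysis lists trend, level, stability, consistency and overlap, then Tau-U. Each describes the shape or replication of the A-to-B change. None bears on why the change starts when it does.

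**The case against.** Several objections carry weight.

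- **The main sentence does not mention placebo.** Maturation, experience, learning and practice read naturally as effects of time in study and repeated assessment, such as practice with the thrice-daily VAS. Staggering addresses these. This stands, so the phrase needs a qualifier and should not be deleted.
- **Contact with the game is not confined to phase B.** The Limitations section describes a mock session before the trial that covers the headset and gameplay. This is correct. One prior session does not, however, change the fact that the daily course, and the hope attached to it, begins with phase B.
- **The game is part of the treatment.** The primary objective concerns the intervention in a gaming environment, so game engagement is a component of the package and not a confounder for that objective. This also stands. Expectation and general session attention remain.
- **The word unbiased may refer only to how baseline lengths are allocated.** That reading is possible. But the sentence attaches it to addressing the effects of the intervention, next to broad wording on confounders.
- **The simulated rates assume the shift that they then detect.** True, and any study without a sham would show the same. The rates indicate scale only; the argument rests on the design.

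A reader might also infer that the plan credits the pain change to altered brain rhythms. It does not say so. On mechanism it says only "we will explore the neural mechanisms underlying the effect of a BCI-N intervention on SCI neuropathic pain", using separate EEG and GABA measures before and after treatment.

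**Conclusion.** The concern holds in a limited form. The Discussion ascribes to the staggered, randomly allocated baselines a general control of bias that they do not have. They control influences tied to calendar time or time in study. They cannot separate expectation and session-related attention from a specific effect, for any size of response.

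This rests on three features of the protocol: participants know when treatment starts, the outcome is self-rated, and no sham or non-contingent phase is described. It does not rest on the simulation, whose shift sizes, SD, autocorrelation and rank test are all assumptions.

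Two stronger readings are not supported. One is that a placebo response would be accepted as proof: Study Design speaks of preliminary effectiveness and the article looks ahead to larger trials, although the Discussion's wording is firmer. The other is that the plan already attributes the A-to-B pain change to band-power modulation; no section does so. The design itself is openly described and can answer the package question. The wording on control and the silence on expectation in the Limitations need correcting.

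**What to change.** 1. **Discussion, Overview.** Replace the controlled-and-unbiased wording with a statement that staggered, randomly allocated baselines control for calendar-time and time-in-study influences. Keep the words on experience, learning and practice, but qualify them as those tied to time in study or repeated assessment.
2. **Limitations and Conclusions.** State that a replicated A-to-B fall estimates the effect of the whole BCI-N package, including expectation and session contact, against no treatment. Add that such a fall cannot by itself be attributed to band-power modulation.

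No procedure, data collection or analysis changes. The cost is a narrower and less favourable conclusion.
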